### Secondary outcomes

Based on the conceptual framework of Shay and Lafata [18], the study will investigate whether the smartphone app will improve the patient’s preparedness for SDM, self-efficacy, patient’s alliance with the clinician, severity of symptoms, level of functioning, hope, and treatment satisfaction. These outcomes will be obtained at baseline and after 6 months. In addition, the feeling of hope, self-efficacy and communication with one’s clinician will be obtained after 3 months.

The Preparation for Decision Making (PrepDM) scale is a self-reported 10-item instrument to measure the patient’s perception of how useful a decision aid or other decision support intervention is in preparing the respondent to communicate with their practitioner at a consultation focused on making health decisions [36]. The questionnaire is rated on a 5-point Likert scale from “Not at all” (1) to “A great deal” (5) with higher scores indicating a higher level of preparedness to communicate with one’s care provider regarding health decisions. The PrepDM has been validated with high internal consistency (Cronbach’s α = .92 to .96) [36]. The PrepDM scale will be translated to Danish for this study using the forward/backwards translation process. The General Self-Efficacy Scale (GSE) measures the patient’s belief that one’s actions are responsible for successful outcomes [37]. The questions consist of 10 items rated on a 4-point Likert scale ranging from “not at all true” (1) to “exactly true” (4) with higher scores indicating higher self-efficacy. The scale has been validated and found reliable in psychiatric care with the Danish version having good internal consistency (Cronbach’s α = .87) [38].

The Working Alliance Inventory-short (WAI) measures the therapeutic alliance between patients and clinicians within three domains; goals; tasks; and bond [39]. The questionnaire consists of 12 items rated on a 7-point Likert scale, with higher scores indicating better working alliance. The scale has been developed in two versions – one for patients and one for provider – and will in this study be filled out by patients and by the primary providers. Providers will fill out the instrument for each of their own patients participating in the study. The scale has good internal consistency (Cronbach’s α = .83–.98) and high correlation with the original WAI [40].

Perceived hope and optimism will be measured using the Adult State Hope Scale (ASH). The 6-item instrument is rated on a Likert-scale from 1 to 8, with higher scores indicating higher levels of hope [41]. The scale has been validated and shows good internal consistency (Cronbach’s α = .93). Psychometrically testing in various settings has shown the scale to be appropriate for self-report on hope and optimism in people with severe mental illnesses [42].

The Perceived Efficacy in Patient-Physician Interactions Questionnaire (PEPPI) is a self-reported 5-item instrument for the assessment of patient’s confidence in communicating with their physician [43]. The questionnaire is rated on a 10-point Likert scale, with higher scores indicating higher perceived efficacy in the interactions. The scale has been found to be valid and reliable in somatic care with excellent internal consistency (Cronbach’s α = .92) [43]. The scale will be translated to Danish for this study using the forward/backwards translation process.

The Client Satisfaction Questionnaire (CSQ) is a self-reported 8-item measure to assess a patient’s satisfaction with treatment. Each item is scored on a 4-point Likert scale, with higher scores indicating higher satisfaction. The CSQ has shown good psychometric properties with a high internal consistency (Cronbach’s α = .93) [44].

The Service Engagement Scale (SES) is a 14-item measurement for the provider to rate their patient’s engagement level on four subscales ‘availability’, ‘collaboration’, ‘help seeking’ and ‘treatment adherence’ [45]. Each item is scored on a 4-point Likert scale, with higher scores indicating poorer engagement. For this study, only the subscale ‘collaboration’ will be used, consisting of 3 questions. The SES has shown good psychometric properties and has previously been used in studies with patients with psychotic disorders [45].

To assess positive and negative symptoms, the Scale for the Assessment of Positive Symptoms (SAPS) and Scale for the Assessment of Negative Symptoms (SANS) will be used. The two scales consist of 3 dimensions: the psychotic, the disorganized, and the negative. Each dimension is scored between 0 and 5 with higher scores indicating higher symptom severity. Social functioning will be assessed using the Global Assessment of Function (GAF) and Personal and Social Performance Scale (PSP). GAF assesses a person’s psychosocial functioning (scores 1–100), with higher scores indicating a higher functioning level. GAF has been found highly generalizable and has been validated as a useful means of assessing global psychosocial health in people with psychotic symptoms [46, 47]. PSP assesses a person’s functioning level within four domains; socially useful activities; Personal and social relationships; Self-care; Disturbing and aggressive behaviors. PSP is scored 1–100, with higher scores indicating a higher functioning level. PSP has been found reliable and valid as a measure of social functioning in patients with schizophrenia [48].

Another aspect of interest is on whether the use of the smartphone app may affect adherence to treatment appointments, medication and/or hospital admissions. To measure this, data on patient adherence to OPUS appointments and number of hospitalizations will be collected from the patient journals while information on the usage of anti-psychotic medication will be collected through the patient interviews.

### Explorative outcomes

To explore the intervention group’s satisfaction of the app, the App Rating Questionnaire (ARQ) will be used in combination with objective data on app usage (user sessions per day, screen views per day, screens per session, session duration and session instances, user retention). The ARQ seeks to capture the end users perceptions of a software application [49]. The scale consists of 4 items scored on a 4-point Likert scale ranging from “Strongly agree” to “Disagree”.

### Data management

All the above-mentioned outcomes except for SAPS, GAF and PSP are either patient- or provider-reported outcome measures and will be collected through self-administered web-based questionnaires. Patients will complete the questionnaires on an iPad provided by the researcher. Questionnaires in paper format will be offered as an alternative. The completion of the questionnaires will be done in the presence of a researcher to clarify any uncertainties participants may have regarding the questionnaires. Questionnaires will be collected and managed using REDCap electronic data capture tools hosted at the The Mental Health Services of the Capital Region [50]. REDCap (Research Electronic Data Capture) is a secure, web-based application designed to support data capture for research studies. REDCap has a complete log and audit trail and complies with Danish legislation on processing personal data. Access to study data will only be available for data managers. Participants will receive an e-mail with a link to the questionnaires. Participants will have to login to a secure portal using a unique password, which is delivered at the patient’s meetings with the researcher. Interview-based data (such as SAPS, SANS, GAF and PSP) will be written directly into REDCap by the researcher. Information on diagnosis, hospital admissions, duration in OPUS treatment and adherence to treatment appointments will be collected retrospectively and retrieved from the patient journals.

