### Randomization and blinding

Randomisation to either the intervention group (TAU + smartphone app) or control group (only TAU) will be performed after baseline assessments. To achieve balance in the allocation of participants to treatment arms and to reduce risk of bias, block randomization of randomly determined block size will be used. To ensure adequate allocation concealment, the procedure will be centralised and computerised with concealed randomisation sequence facilitated by Odense Patient data Explorative Network (OPEN). Investigators will contact the randomisation unit, OPEN, with the necessary information to conduct the randomisation after baseline data have been collected.

Given the nature of the intervention, patients and healthcare providers cannot be kept blinded. Investigators responsible for data collection and data entry will be blinded as to patient allocation until all outcomes have been collected. Participants are given an identification number to ensure that the research team involved in data management are unaware of the treatment allocation. All patients are at each visit with the researcher thoroughly instructed not to mention anything about randomization allocation.

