### Assessments

Communication between patient and provider (including SDM) may lead directly to improved health outcomes but more often communication affects health outcomes indirectly [18]. For instance, a SDM intervention could improve treatment satisfaction resolving in a promotion of health behaviour which lastly may end up improving different important health outcomes (e.g. reduction of symptoms). The conceptual framework by Shay and Lafata describes the link between SDM and affective-cognitive outcomes (e.g. alliance and satisfaction), behavioural outcomes (e.g. activation or engagement) and health outcomes (e.g. symptom reduction) [18]. Therefore, these areas will be measured during the intervention. Patient activation (behavioural outcome) was chosen as our primary outcome because of our intervention being primarily patient-centred. Prior to the data collection, we conducted a pilot study in OPUS with 8% of our proposed sample size (21 patients) to test the primary outcome (CHAI-MH). Furthermore, all questionnaires were tested with patients from OPUS to ensure that questions were understandable and unambiguous. The pilot test showed no ceiling effects or issues regarding the understanding of the questionnaires.

Participants will be assessed at three-time points: at baseline, after 3 months and after 6 months (end of intervention). Clinicians will be assessed at baseline and when each of their participating patients completes the 6 months intervention period. In case of non-respondents, participants will be contacted after 2 weeks with a reminder to complete the survey.

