A limitation for this study is the lack of qualitative data. Qualitative interviews performed after the intervention to explore the participants’ experiences of the smartphone app in relation to SDM is being considered. Observational measures on the interactions between patient and provider to observe potential changes in the decision-making process and on how the app is used in the consultations would be meaningful. If feasible, interviews and observational measures will be performed after the end of the intervention. Although patients and providers are encouraged to include the smartphone app in the consultations when relevant, it is unknown to what extent this will happen. To address this, patients in the intervention group will be asked at the end of the intervention approximately how often they included the app in the consultation and whether it was the patient or the provider who took the initiative to include the app. Although OPUS is a well-established treatment site, OPUS was chosen as our study site due to providing a high feasibility for conducting research studies and due to our pilot study indicating that younger adults with schizophrenia-spectrum disorders indicate that an easy accessible solution, such as the smartphone app presented in this trial is a relevant tool to better prepare for treatment consultations and to take a more active role in the treatment [32]. Patients receiving OPUS treatment meet with several staff members. Still, we chose only to focus on the primary provider due to the fact that a patient in OPUS meets their primary provider significantly more often than any of the other staff members (e.g. the psychiatrist).

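### App-only questionnaires are to be completed with a researcher present, which conflicts with the promise that data collectors stay blinded until all outcomes are in

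*Protocol article*

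**What the plan says.** Under Randomization and blinding, the protocol article accepts that patients and providers cannot be blinded, and sets the rule for research staff: "Investigators responsible for data collection and data entry will be blinded as to patient allocation until all outcomes have been collected". The safeguard it gives for study visits is an instruction to patients: "All patients are at each visit with the researcher thoroughly instructed not to mention anything about randomization allocation".

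Under Explorative outcomes, one instrument belongs to one arm only: "To explore the intervention group’s satisfaction of the app, the App Rating Questionnaire (ARQ) will be used". The Discussion adds a second set of one-arm items: "patients in the intervention group will be asked at the end of the intervention approximately how often they included the app in the consultation", together with who took the initiative to include the app. Under Assessments, the end of the intervention is the 6-month visit, which is also the last assessment.

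Data management follows the outcome sections and describes collection. It opens: "All the above-mentioned outcomes except for SAPS, GAF and PSP are either patient- or provider-reported outcome measures", and says these are collected by self-administered web questionnaire. Patients use an iPad that the researcher provides, with paper as an alternative. It continues: "The completion of the questionnaires will be done in the presence of a researcher to clarify any uncertainties participants may have regarding the questionnaires". The same section mentions an e-mailed link with a personal login, and says that the researcher enters the SAPS, SANS, GAF and PSP ratings directly into REDCap.

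**The concern.** Two stated procedures do not fit together. One blinds everyone who collects or enters data until the last outcome is in. The other places a researcher beside the patient, ready to answer questions about the items, while the patient completes a set of forms that includes one only the app arm can answer. A patient who asks what an ARQ item means discloses allocation without breaking the instruction to keep silent about it, and so does an app-rating form visible on the iPad.

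What is at stake is the protection that observer blinding can give here. Patients and providers know the allocation, so their own ratings are open to expectation effects whatever the researchers know. Blinding of researchers matters mainly for what researchers score: the three SAPS/SANS dimensions, GAF and PSP. It matters to a lesser degree for information that they gather by interview or from patient journals, such as antipsychotic use and hospital admissions. The researcher-scored outcomes are secondary outcomes tested at 0.05. The primary outcome, CHAI-MH, is scored from the patient's own answers.

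**Working it through.** **Setting the sections side by side**

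1. *Is the ARQ within the rule on researcher presence?* Data management applies to all outcomes mentioned before it, apart from the interview scales. Explorative outcomes comes immediately before it, so the ARQ is covered. No exception for app-only forms is stated.
2. *Does the ARQ distinguish the arms?* Yes. It is introduced as a measure of the intervention group's satisfaction with the app, and controls do not receive the app.
3. *Are the app-in-consultation questions covered?* They are restricted to the intervention group and timed at the end of the intervention. They appear only in the Discussion and no mode of asking is given, so nothing routes them through the researcher and nothing keeps them away.
4. *Does the silence instruction close the gap?* No. It governs what patients say about allocation, not which forms they are given or which item queries they raise.
5. *Is the attending researcher the rater?* The section refers to a researcher for the questionnaires and to the researcher for the interview data, and names no separate unblinded role. This suggests one person but does not say so. The blinding rule covers all data collectors, so the conflict exists either way; bias in the ratings needs the same person or shared knowledge.
6. *Does exposure come before rating?* The order within a visit is not given. If the ARQ is given at 6 months and the interview comes first, that patient's ratings are safe, because no later rating exists. If the ARQ is given at 3 months, exposure would precede the 6-month ratings. The readable text gives the ARQ no time point, and the schedule in Table 1 is not reproduced.

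**Illustrative size**

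The plan gives no figure on this point. The illustration needs the number of completers per arm, which comes from Power and sample size. That calculation reproduces: effect size 0.42, two-sided alpha 0.05 (sidedness assumed) and 80% power give 89.96, so 90 per group by the t-test. With 30% dropout, 90/0.70 = 128.6, so 129, against the 130 planned. Expected completers are 130 × 0.70 = 91 per arm.

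Suppose there is no true effect and knowledge of allocation shifts the app-arm mean rating by b standard deviations. Then:

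- Standard error of the difference = √(2/91) = 0.148 SD.
- Probability of a significant result in the direction of the shift ≈ 1 − Φ(1.96 − b/0.148). The opposite tail adds less than half a percentage point for the shifts below.

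| Assumed mean shift b | b/0.148 | Chance of a false significant result |
|---|---|---|
| 0 (ratings precede exposure) | 0 | 5% (both tails) |
| 0.1 SD | 0.67 | about 10% |
| 0.2 SD | 1.35 | about 27% |
| 0.3 SD | 2.02 | about 53% |

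Here b is the average over the whole app arm. If only half the patients were exposed and each exposed rating moved by 0.2 SD, b would be 0.1. No value of b can be taken from the documents.

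**The case against.** The strongest reply is that a journal article leaves form order and staffing to the full protocol. The questionnaires are self-administered behind a personal login, the researcher is there to clarify rather than to read answers, and an e-mailed link exists. Non-respondents get a reminder after two weeks, which suggests that some completion happens away from the visit. No single item is shown in the readable text to be both timed at 6 months and completed with the researcher present: the ARQ has the setting without the time, and the app-in-consultation questions have the time without the setting. Only secondary outcomes are exposed.

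Most of this stands as a limit on the claim. It does not remove the conflict, because the article does not merely omit detail: it states a presence rule that includes the ARQ, and a blinding rule that the presence rule can defeat. Nor does it say that remote completion replaces researcher presence.

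Stronger readings that a reader might infer are not supported:

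- *Every app-arm completer is revealed to the rater.* Presence creates a risk of exposure, not certain exposure, and the identity of the rater and the order of events are not stated.
- *PrepDM also gives allocation away, because it refers to decision support.* It is a secondary outcome compared between arms, so both arms complete it and receiving the form does not distinguish them.
- *The app-usage logs unblind the raters.* The article does not say who holds the logs or when they are merged, and it does not say that data managers rate patients.

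**Conclusion.** The concern holds as a conflict between stated procedures. Followed as written, the data-collection procedure can reveal allocation to staff whom the article says are blinded, and the stated visit safeguard does not address that route. Bias in the 6-month SAPS/SANS, GAF and PSP ratings is a possible consequence. It requires that the attending researcher is the rater or informs the rater, that this person sees or is asked about app-only items, and that this happens before the ratings are entered. None of the three is stated.

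The false-positive rates of 10% to 53% depend on assumed shifts of 0.1 to 0.3 SD and on 91 completers per arm. They show why the matter deserves attention and are not an estimate of what will happen. The effect is confined to outcomes that researchers score or gather; scoring of CHAI-MH is not directly touched, and the sample size is not in question.

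**What to change.** Reconcile Randomization and blinding, Explorative outcomes, Data management and the Discussion by adding two rules:

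1. At 6 months, the SAPS, SANS, GAF and PSP ratings are completed and locked in REDCap before any app-only item is shown.
2. The ARQ and the app-in-consultation questions are always delivered without the blinded researcher, at whichever visit they fall. The e-mailed link already planned would serve, sent after the visit; a team member with no rating role is an alternative.

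The second rule is needed as well as the first, because an ARQ given before the 6-month visit would not be covered by ordering forms within that visit.

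The cost is a change in REDCap form order and a short instruction to staff, with slightly lower ARQ completion when it is answered remotely. Inclusion began in January 2019, so 6-month visits start from about July 2019. The rules should be in place before then, because blinding once lost cannot be restored.

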### Power and sample size

The power calculation is based on the results of 6 RCT studies investigating patient activation using the Patient Activation Measure as a primary outcome [51–56], and by using the PS Power and Sample Size Calculations program version 3.1.2. This was done due to a lack of RCTs using the CHAI scale. While these studies use a different scale, they do measure the same domain: patient activation. We calculated our planned sample size based on the effect size on patient activation for these 6 studies. These studies had a mean effect size of 0,42, ranging from 0,28 – 0,65. Based on these studies, we expect to find an effect size between our intervention and control group of 0,42. To reach a power 80% and alpha of 0,05 we will need 90 participants in each group to be able to reject the null hypothesis that the population means of the two groups are equal. We plan on having 1 control per intervention subject. With an expectation of approximately 30% dropouts, we will include 130 participants in each group for a total of 260 participants. In addition, we performed sample size calculations for several secondary outcomes. None of these calculations exceeded 260 participants to detect a significant statistical difference for some of our secondary outcomes as well as our primary outcome.

### Statistical analysis

The analysis will be performed by using the IBM SPSS and SAS. Significance levels below 0,05 will be considered significant for the analysis of primary and secondary outcomes.

The data analysis will be conducted accordingly to the principle of intention-to-treat (i.e. patients will be included in the analysis according to group assignment even if they do not receive all of the planned intervention). In case of missing data, the operation of multiple imputations will be used to address the issue of missing values. To validate the complete case analyses, an analysis of the drop outs will be conducted.

With multiple assessment points, we will use mixed-effects linear regression for the primary analysis. The mixed-effects model is chosen to account for the dependency inherent in the data due to repeated measurements and to allow respondents with missing observations at different time points. If relevant, subsequent statistical tests will be performed. Cohens Kappa will be performed to determine the level of agreement between the patients and providers..

If any of our outcomes do not meet the assumptions for parametric statistical tests, data will either be transformed as appropriate prior to analysis or replaced by non-parametric statistical tests.

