## Discussion

The Momentum trial is to our best knowledge the first randomized controlled trial to evaluate the effectiveness of a smartphone application to engage people with schizophrenia-spectrum disorders in their treatment consultations to support patient activation and SDM. The intervention will focus on supporting patients through the smartphone app to become more active in their care (primary outcome). In addition, the intervention will also connect patients together with their providers (through a web portal) to gain a common starting point before treatment consultations. We expect that the combination of patients becoming more active in their care together with having their data shared with the provider will improve the patient’s preparedness for SDM, the therapeutic alliance, the efficacy of therapeutic interactions, hope, self-efficacy, severity of symptoms and level of functioning (secondary outcomes).

A major strength of the study is the comprehensive pilot study prior to the trial. While the trial is primarily focusing on quantitative assessments, the pilot study was mainly qualitative with a focus on identifying needs and preferences in the target group in relation to a smartphone app to support SDM. Another strength of the study is the focus and assessment on both patient and provider. Research indicates that addressing data from patients and providers together may yield more powerful effects than only focusing on one of the two [8]. Information from both perspectives will also provide valuable information on how patients and providers view their alliance. In addition, providers will be asked to rate the patient’s engagement level to compare this with the patient’s own perceived level of engagement. Finally, we have a solid sample size calculation to perform a data analysis with good strength regarding our primary outcome and several secondary outcomes.

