If the Momentum trial confirms the hypothesis that providing people with schizophrenia-spectrum disorders with the presented system will increase their level of activation in the treatment and support SDM, the study will provide evidence on the effects of using such tools to support people with severe mental illness in engaging in their own healthcare management. In addition, the study may provide evidence to the idea that linking client and practitioners in digital solutions can have advantages in facilitating SDM in mental health. Overall, the study will provide more evidence to the further developing and implementation of electronic tools to support SDM in mental health care. Future enhancements will be to integrate the smartphone app with the existing IT systems and to investigate its efficacy long term (> 1 year) and in other mental healthcare settings.

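### About 16 secondary endpoints may each be called significant at an unadjusted 0.05, with no gate behind the primary, although the SDM half of the intended conclusion rests on secondaries alone

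*Protocol article*

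**What the plan says.** The significance rule in the Statistical analysis section covers both tiers of outcome: "Significance levels below 0,05 will be considered significant for the analysis of primary and secondary outcomes". That section states no hierarchy and no adjustment, and does not require the primary to succeed first.

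The Methods/Design section states a main hypothesis on CHAI-MH at 6 months and a directional secondary hypothesis over eight domains. The article also has a separate Explorative outcomes section, so the secondaries stand above an exploratory tier. In the Discussion, the conclusion that the trial hopes to reach is that the system "will increase their level of activation in the treatment and support SDM".

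On secondary power, the Power and sample size section says: "None of these calculations exceeded 260 participants to detect a significant statistical difference for some of our secondary outcomes". The Discussion lists as a strength that the sample size allows the team to "perform a data analysis with good strength regarding our primary outcome and several secondary outcomes".

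**The concern.** CHAI-MH measures patient activation. Preparedness for SDM, communication with the provider, alliance and collaboration are all secondary outcomes, so the SDM part of the conclusion can come only from them. Under the stated rule any one of them may be declared significant at 0.05, however many are tested and whatever the primary shows. With this many tests, one chance result is likely enough that a reported SDM benefit could be noise.

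The plan fixes this rule itself. It is not a gap left for a later analysis plan, because an analysis plan that ranked or adjusted the secondaries would contradict the article.

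**Working it through.** **1. The plan's own sample size.** Inputs from the Power and sample size section: effect size 0.42, 80% power, alpha 0.05 (taken as two-sided), 1:1 allocation, 30% dropout.

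- n per group = 2 × (1.960 + 0.842)² / 0.42² = 89 by the normal formula. The t-test version gives 89.96, so 90, as stated. A one-sided test would give 71 and does not match.
- 90 / (1 − 0.30) = 128.6, so 129, against 130 stated.
- Expected completers: 130 × 0.70 = 91 per arm, 182 in all. Power for 0.42 at 91 per arm is about 80% to 81%.

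The primary calculation is sound.

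**2. Counting the secondary endpoints** (Secondary outcomes section):

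| Group | Endpoints | Count |
|---|---|---|
| Questionnaires | PrepDM, GSE, WAI patient, WAI provider, ASH, PEPPI, CSQ, SES collaboration | 8 |
| Symptoms | psychotic, disorganized and negative dimensions | 3 |
| Functioning | GAF, PSP | 2 |
| Service use and medication | appointment adherence, hospitalisations, antipsychotic use | 3 |
| Total | | 16 |

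Hope, self-efficacy and communication are also measured at 3 months. These repeats are left out of the count.

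**3. Chance of at least one false positive if every null hypothesis is true.** For k independent tests this is 1 − 0.95^k. For correlated tests it was simulated with equicorrelated normal test statistics (400,000 draws, two-sided 0.05). The documents give no correlations, so 0.3 to 0.7 is an assumed range.

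| Family | Independent | Correlation 0.3 | 0.5 | 0.7 |
|---|---|---|---|---|
| All 16 endpoints | 56% | 48% | 37% | 26% |
| Eight domains, one test each | 34% | 30% | 25% | 19% |

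The expected number of false positives among 16 is 16 × 0.05 = 0.8.

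For the five measures closest to SDM (PrepDM, PEPPI, WAI patient, WAI provider, SES collaboration), 1 − 0.95⁵ = 23% if independent, and less if positively correlated.

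**4. The secondary power statement.** The article does not name the outcomes, give their inputs or say whether their totals include dropout. Two cases follow.

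- If dropout is already included, 260 is the right benchmark and nothing is lost.
- If it is not, a patient-reported outcome should be compared with about 182. In the extreme case an outcome needs exactly 260 analysed. Its detectable effect is (1.960 + 0.842) × √(2/130) = 0.347. With 91 per arm, 0.347 × √(91/2) − 1.960 = 0.38, which gives about 65% power. An outcome needing 182 or fewer keeps at least 80%.

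**The case against.** **Single primary.** The trial has one primary outcome at one time point, and unadjusted secondaries behind a single primary are common practice. This is true, and a reader should not infer that the type I error of the primary is inflated. But common practice treats such secondaries as supportive. Here they carry a directional hypothesis, sit above an exploratory tier and share the primary's significance rule.

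**Size of the risk.** It is tempting to read 56% as the chance of a false SDM claim. It is not. It assumes independence, which is implausible for pairs such as GAF and PSP. Most of the 16 are also not SDM measures: a chance result on hospitalisations would say nothing about SDM. The figure that fits the SDM claim is about 23% or less.

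**Failed primary.** A reader might infer that one chance secondary would rescue a failed primary. The Discussion does not say so: its conclusion is conditional on the hypothesis being confirmed and joins activation with SDM support. What remains is that a secondary may still be labelled significant on its own, and that the SDM half of the joint claim has no error control.

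**Power.** A reader might infer that all 16 outcomes are claimed to be powered, or that secondary power is overstated because 260 was used where 182 was needed. The documents support neither. The article speaks only of several or some secondary outcomes. Its 260 is already the dropout-inflated total for the primary, so the secondary totals may be inflated in the same way. Nor is 182 the planned analysis set: intention-to-treat, multiple imputation and the mixed model keep all randomised patients, although the 6-month information on patient-reported outcomes may be near that of 182. Outcomes taken from patient journals or rated by providers need not fall to 182 at all.

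**Conclusion.** The multiplicity point holds. The plan allows an unadjusted, ungated significance claim on each of about 16 secondary endpoints. The chance of at least one false positive is 26% to 56% over all 16, 19% to 34% over the eight hypothesised domains, and up to about 23% over the five SDM-related measures. These figures assume that all the nulls in the family are true and that the tests are independent or positively correlated at the values shown. The primary analysis and its sample size are unaffected.

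The power point is only a request for clarification. Power as low as about 65% arises only if dropout was left out and an outcome needed exactly 260 analysed patients.

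**What to change.** Change the rule in the Statistical analysis section as follows.

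1. The confirmatory claim is CHAI-MH at 6 months, tested at 0.05.
2. One SDM-related secondary, named in advance and measured validly in both arms, is tested at 0.05 only if the primary succeeds. PEPPI is a suitable example. PrepDM is less suitable, because it asks how useful a decision aid or support was and control patients receive no app.
3. All other secondaries are reported as estimates with 95% intervals, labelled supportive, without significance claims.

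With this fixed order, the chance of any false confirmatory claim is at most 5%, and so is the chance of a false confirmatory SDM claim.

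In the Power and sample size section, state which secondary outcomes were calculated, and whether their totals include the 30% dropout. If they do not, compare the patient-reported ones with about 182 expected completers.

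The cost is wording and one restated sentence. The downside is that fewer secondaries can be called significant, and that the SDM claim depends on the primary succeeding first. If the second test also had 80% power and were independent of the first, both would succeed with probability 0.80 × 0.80 = 64%. Positive correlation would raise this, to at most 80%.
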